### 7.12 CARDIAC MAGNETIC RESONANCE (APPENDIX V)

Cardiac magnetic resonance scanning will be performed in accordance with the CMR sub-study criteria at day 7+/- 3 days. It is anticipated that the CMR sub-study will be performed in a limited number of the participating sites that have easy access to scanning facilities to avoid recruitment bias. Key outcome measures for the CMR sub-study are infarct size, the number of discrete MI (Type 4a), myocardial salvage, the presence and extent of microvascular obstruction, LV volumes and ejection fraction criteria.

Participants will be paid reasonable travel expenses to the sum of £15 for attending the CMR scan visit.

### 7.13 BIOMARKERS SUBSTUDY (APPENDIX VI)

A substudy testing selected novel biomarkers will be performed in accordance with the Biomarkers substudy protocol attached in Appendix VI. It is anticipated that the Biomarkers substudy will be performed in selected sites. Key outcome measures for the substudy include the predictive ability of the selected biomarkers for obstructive coronary artery disease and requirement of PCI, and main trial clinical outcome measures.

### 7.14 FOLLOW-UP

Patients will be informed that they should contact their general practitioner if they develop any problems during the course of the study. In general a second anti-anginal agent (e.g. long-acting nitrate/Nicorandil/calcium channel blocker) should be considered before

RAPID-NSTEMI[figure not shown]

non-invasive imaging with or without angiography are considered. Patients with major or persistent symptoms will be referred back to the clinical team for review. In this study it is recommended that symptoms are investigated by non-invasive imaging to confirm the likelihood that they are due to myocardial ischaemia, prior to consideration of angiography (+/-). Revascularisation is allowed with ongoing CCS class III symptoms with a negative ischaemia test, if symptoms persist despite 2 anti-anginal medications at maximum tolerated doses. In the event of a further acute coronary syndrome it is anticipated most will undergo repeat angiography.

**Follow up at 30 days +/- 1 week**

Patients will be contacted by telephone at 30 days +/- 1week. Information on clinical progress and especially on readmission, further investigations, EQ-5D-5L and Seattle Angina Questionnaire and changes to medication will be documented. A complete list of medication being taken will be recorded.

**Follow up at 6 months +/- 2 weeks**

Patients will be contacted by telephone at 6 months +/- 2 weeks. Information on clinical progress and especially on readmission, further investigations, EQ-5D-5L and Seattle Angina Questionnaire and changes to medication will be documented. A complete list of medication being taken will be recorded.

**Follow up at 12 months +/- 4 weeks**

Patients will be reviewed in a research clinic at 12 months +/- 4 weeks, and the following tests and outcomes will be recorded for all patients in the randomised study. ECG, echocardiogram, EQ-5D-5L form, Seattle Angina Questionnaire document clinical status and especially any re-admission, the reasons for re-admissions, further investigations and further procedures, any changes in medication. Where sites are not undertaking an echocardiogram or ECG at 12 months or a patient is unable to attend the 12 month clinic visit, outcome data will be collected by telephone.

Participants will be paid reasonable travel expenses to the sum of £15 for attending the 12 month clinic visit.

**7.15 CLINICAL EVENT REPORTING****7.15.1 General Potential Risks and Hazards to patients**

Fundamental patient risks are standard as both arms receive standard treatment. There are no trial drugs nor devices being tested. This is a strategy trial. The potential risks to all patients are related to those from the PCI procedure: risk of 0.5% Death/MI/CVA/need for emergency CABG, 1% risk of vascular injury. The risk/benefit associated with delay to standard of care time compared to immediate intervention has never been compared, especially in the era of contemporary agents and indeed is the primary conceptual objective of this trial. Any bleeding or vascular complications will however be immediately identified by clinical teams and appropriate clinical management strategies employed as per all routine N-STEMI post-PCI patients. All events will be reported timely as adverse events (AE) or serious adverse events (SAE) as per routine trial governance. There will be TMC, DSMC and CEC oversight. For the CMR sub-study, patients with advanced impaired renal function will not be approached due to risk of Nephrogenic Systemic Fibrosis.

RAPID-NSTEMI[figure not shown]

Early stopping: The DSMC will meet on a regular basis (determined by the Independent chair) and they will review data provided by an independent statistician and decisions will be made as to whether the trial should be discontinued, early for safety concerns. We will positively discourage stopping for futility/interim +ve study result. In the event the trial is stopped early, all patients recruited to that point will continue to be followed for the duration of the follow-up period.

**7.15.2 ADVERSE EVENTS**

All adverse events will be collected from randomisation until discharge from hospital. Thereafter only adverse events deemed serious or those listed as an expected SAE's or a pre-specified clinical outcome measure (see section 7.1.5) will be collected until the end of the trial.

**7.15.3 Definitions of Adverse Events**

Defined as any untoward medical occurrence

**7.15.4 Definitions of Serious Adverse Events (SAE)**

A Serious Adverse Event (SAE) is defined as any untoward medical occurrence that:

- Results in death
- Is life-threatening

NB: The term "life-threatening" in the definition of "serious adverse event" refers to an event in which the patient was at risk of death at the time of the event; it does not refer to an event which hypothetically might have caused death if it were more severe.

- Requires hospitalisation or prolongation of existing inpatient's hospitalisation
- Results in persistent or significant disability or incapacity
- Results in a congenital anomaly or birth defect

**7.15.5 Expected serious adverse events/clinical outcomes**

Some serious adverse events occurring in this trial will be expected as a consequence of the underlying disease, routine treatments or diagnostic tests or study related investigational procedures. In addition, the pre-specified clinical outcome measures in the study will not be considered SAEs. The eCRF will be designed to capture expected clinical outcomes.

Expected serious adverse events that do not require expedited reporting are:-

- Death
- Myocardial infarction
- Recurrent ischemia
- Stroke
- Heart failure
- Cardiogenic shock
- Cardiac rupture or tamponade
- Ventricular septal defect
- Valve regurgitation
- Vascular trauma related to PCI procedure
- Arterial or venous embolic events
- Minor and major bleeding

RAPID-NSTEMI[figure not shown]

- Revascularisation procedure (PCI or CABG)
- Hospital admission for a cardiovascular cause
- Renal impairment due to pre-existing renal disease and/ or contrast load during angiogram
- Haematoma at angiogram/PCI access site
- Arrhythmias (supraventricular or ventricular)
- Contrast induced confusion post angiogram
- Admission or procedure for a pre-existing condition

All of the expected SAEs listed (not requiring expedited reporting) should be reported via the eCRF within one week of knowledge of the event.

### 7.15.6 Classifying SAEs

All SAEs will be assessed for causality and relationship to trial.

- Related events are those that are considered to have resulted from the administration of any research procedures. These include PCI, CMR, and myocardial perfusion scanning.
- Unrelated events are those that are not listed in this protocol or the participating sites clinical patient information sheets for procedures.

### 7.16 SAE REPORTING

Sites will be required to report all unexpected SAEs to the Coordinating Centre via email within 24 hours of identification of the event; a corresponding eCRF should be submitted to MACRO EDC at the earliest possibility. The Coordinating Centre will provide a monthly SAE line listing to the Sponsor, and escalate any priority issues to the Sponsor as required. Investigators will be required to identify if the event is related to the trial. A summary of safety will be included in the annual progress report to the Ethics committee.

Expected SAEs (as listed in 7.15.5) do not require reporting directly to the Coordinating Centre, but should be submitted via MACRO EDC at the earliest opportunity, within one week of awareness.

### 7.17 END OF TRIAL

The trial will end when all patients have completed the observation period (i.e. when the last patient recruited has completed the 12 month follow-up assessment). Longer term “passive” follow up will continue through NHS Digital. Consent for this will be obtained from patients for a period for up to 10 years.

### 7.18 WITHDRAWAL

Participants may leave the trial by withdrawing their consent to participate at any time for any reason, without compromising the medical care they will receive in relation to the trial. Participants do not have to give a reason for withdrawal but if they provide a reason for leaving the trial this will be documented in the CRF. Any data collected prior to the withdrawal may be used in the final analysis.

RAPID-NSTEMI

[figure not shown]

8.0 STATISTICAL ASPECTS

8.1 Power calculations

The power calculations are based on the results of several studies including the retrospective TIMACS study (11,22). Subsequently a post-hoc analysis using GRACE score was applied - patients with a GRACE risk score of >140 (equating to the third with the highest risk) in the early-intervention group had a primary outcome 13.9%, and in the delayed group of 21.0%, a reduction of 35% at 6 months. (HR=0.65; 95% CI, 0.48-0.89; P=0.006). We have decided to include admission for heart failure since there is clear evidence that this is an important outcome following admission with N-STEMI ACS (27) with rates between 5.6% (28) and 15% (29). The best data on new heart failure comes from Kaul (30) who reported a 12.8% incidence.

We have also calculated outcomes based on imputing data into the GRACE score 2.0 and on review of all data, concluded that a GRACE 2.0 score of ≥118 or ≥90 with further high risk clinical factors provides similar outcomes to the proposed event rates. Those with the intermediate GRACE 2.0 risk score (i.e. ≥90) are included providing they have one other high risk features not captured by GRACE 2.0 namely anterior “infarction”, ST segment depression, diabetes (on medication) and a Hs Troponin rise > 3x ULN.

Both the GRACE 2.0 of ≥118 or the GRACE 2.0 ≥90 with one of the risk factors, together with the heart failure data, will provide patient with an event rate ~19%.

Since outcomes have improved somewhat over recent times we have powered RAPID-NSTEMI conservatively to detect a 25% reduction in the composite primary end point.

Standard intervention arm (Group B), predicted primary outcome events = 19%.

Immediate Intervention arm (Group A) predicted primary outcome events = 14.25% (odds ratio of 0.71, relative risk reduction of 25%).

|                                       |        |
|---------------------------------------|--------|
| Effect size (relative risk reduction) | 25%    |
| MACE rate standard PCI group          | 19%    |
| MACE rate Immediate PCI group         | 14.25% |
| Number of patients per group          | 964    |
| Total number of patients in study     | 1928   |
| Total number including 5% drop out    | 2314   |
| 5% crossover and 8% CABG treatment.   |        |

To achieve a power (1-β) of 80% with a (two sided) α=0.05, 964 patients are required in each arm. Assuming up to 5% drop-outs, 5% crossover, 8% needing CABG 1157 patients will be recruited to each of the treatment arms A and B, leading to a total of 2314 patients. (Risks to complete recruitment **APPENDIX VI**).

Based on the above, we consider the power calculations to be conservatively robust and the proposed sample size of sufficient power to detect a significant (and clinically important) reduction in primary endpoint. The calculations have been performed in STATA v14 using the  $\chi^2$  test of equal proportions with the support of the proposed trial statistician.

The trial will follow an adaptive design with closed DSMC review of standard of care event rates.

RAPID-NSTEMI[figure not shown]**8.2 STATISTICAL ANALYSIS PLAN**

Statistical analyses will be undertaken according to a pre-trial Statistical Analysis Plan (SAP) which will be prepared by the statistician employed on the study. Descriptive characteristics at baseline will be presented by treatment arm.

The Primary endpoint is composite outcome of major cardiovascular events (MACE–Death/MI/admission with heart failure) within 12 months, and secondary analyses will be performed for MACE at 30 days following identical methodology. All analyses will be performed following the intention-to-treat principle, with subsequent “immediate follow-on revascularisation” secondary analyses. The primary analysis will investigate the proportion of participants having a primary outcome in each arm, with OR and 95% confidence interval calculation. Additional analyses will compare events in Group A and B with a “time-to-event” endpoint of the primary outcome occurring up until 12 months. Two-sided 95% confidence intervals will be presented for the primary endpoint and all secondary end-point comparisons between groups. The detailed statistical analysis plan will be produced and agreed with the Trial Steering Committee, Sponsors and trial funders prior to trial initiation. The trial will be registered with [clinicaltrials.gov](https://clinicaltrials.gov).

A methods paper outlining the trial will be sent to an appropriate recognised journal for publication.

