#### 6.5 HYPOTHESIS TO BE TESTED

RAPID-NSTEMI will test the following hypothesis:

Immediate angiography with a view to follow on revascularisation in patients presenting with N-STEMI ACS and at higher risk (GRACE score  $\geq 118$  or  $\geq 90$  with additional high risk features), will result in a significant reduction in rate of major adverse clinical outcomes

RAPID-NSTEMI[figure not shown]

(death/MI/hospitalisation for heart failure) within 12 months compared with angiography with follow on revascularisation undertaken according to current standard of care.

Randomisation will take place prior to angiography, following GRACE 2.0 score assessment. At angiography it will become clear that a percentage of patients will require CABG (~8%), some will have normal coronary arteries and some will be treated medically but the analysis will be on an intention to treat (ITT) basis, since randomisation needs for logistical reasons to be undertaken prior to angiography. While the final analysis will be ITT, outcomes according to actual treatment received will also be reported separately as a “per treatment received” analysis.

This will be very important since it will test the hypothesis as to whether very early received intervention is better than current standard of care. Thus, a secondary analysis will be those who receive revascularisation at the time of very early angiography versus those who receive revascularisation at the timing of current standard of care.

We expect this to be a Guideline-informing, clinical practice-directing trial that will help direct clinicians as to the timing of PCI in N-STEMI ACS patients. The trial is didactic, simple, robust, and will be managed by experienced interventional trialists and a registered Clinical Trials Unit, all with a track record for trial delivery.

RAPID-NSTEMI[figure not shown]

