### **4. Statistics and power calculations**

#### **Sample size**

With the available resources we will be able to collect and analyse two samples (pre and post-angiography) from 550 patients. It is expected that approximately two-thirds of patients in our cohort will require PCI. If we recruit 550 patients, we expect approximately 367 to require PCI and 183 to not. Based on these 550 patients, 80% power and a 5% significance level, we can calculate the following for the three novel biomarkers.

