## APPENDIX VII Risks to recruitment

### Compliance and loss to follow-up.

The main risk to completing this trial and its robust interpretation will be inappropriately delayed PCI in the very early group and/or early over enthusiastic intervention in the standard arm group with “time contamination”. Study discipline is essential.

Other risks include loss to follow-up and patient withdrawal from the study. We have accounted for a potential loss-to-follow-up rate of 5% in our power calculations. The sample also includes those who randomised to standard treatment require urgent intervention (ie crossovers). In addition, some patients may be referred for CABG instead of undergoing PCI if there is evidence of complex lesion anatomy or multi-vessel disease with high SYNTAX score. Again, we estimate from the ABOARD study that this should be ~8% of patients. Furthermore some (a few %) will have normal coronary arteries and others will need to be treated medically (diffuse disease). While all patients randomised to the study will be analysed with “intention to treat” analysis, there will also be a subsequent analysis according to the actual hypothesis being testing: comparing trial treatment received (very early intervention with delayed/standard intervention).

Regarding the recruitment risk to the project, there is always a potential risk of lack of up-take or slow recruitment rate from the participating sites. Thus, we will arrange for 3 regional study-related investigator meetings (Glasgow, Southampton and Oxford) to which 2 members of each centre (PI and research nurse) will be invited to go over trial logistics and recruitment. The clinical research fellow employed for the study will be the important co-ordinator and will work closely with the trial manager to provide regular updates on recruitment rates to participating sites to encourage recruitment. The use of a per-patient recruitment fee should also encourage recruitment to the study by participating sites. This is a portfolio study so will have NIHR funded nurse support.

We will be initiating recruitment in 5 large sites to give the trial a positive kick start.

[figure not shown]

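### Section 8.1 inflates the sample size for crossover and CABG as if those patients were lost, but the intention-to-treat analysis keeps them, so the stated 80% power does not follow from the stated allowances

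*Protocol*

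**What the plan says.** Section 8.1 of the protocol predicts primary-outcome rates of 19% in Group B and 14.25% in Group A, a 25% relative reduction, and tests them with a chi-squared comparison of proportions. It states: "To achieve a power (1-β) of 80% with a (two sided) α=0.05, 964 patients are required in each arm". It continues: "Assuming up to 5% drop-outs, 5% crossover, 8% needing CABG 1157 patients will be recruited to each of the treatment arms A and B", for a total of 2314. In the accompanying table, the row giving 2314 is labelled "Total number including 5% drop out", and the crossover and CABG percentages appear in the row below. The section then describes the calculation as conservative and robust.

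The analysis population is set out elsewhere. Section 6.5 expects about 8% of patients to need CABG and some to have normal arteries, and adds: "some will be treated medically but the analysis will be on an intention to treat (ITT) basis". Section 8.2 applies the intention-to-treat (ITT) principle to all analyses, and Appendix VII repeats that all randomised patients are analysed that way. Appendix VII identifies the 5% as loss to follow-up and the crossovers as Group B patients who need urgent intervention. Section 7.8 counts both PCI and CABG as revascularisation decided at angiography.

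**The concern.** A head-count inflation replaces patients whose outcomes will not be in the analysis. That suits the 5% lost to follow-up. It does not suit patients who cross over or have CABG, because their outcomes are counted in the arm to which they were randomised.

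There are two coherent ways to treat those patients:

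- If the 25% reduction applies only to patients treated as assigned, the others shrink the arm-level difference. The required sample then grows with the inverse square of the share of the effect that remains.
- If the 25% reduction is already the difference between the randomised arms, they are inside it and need no allowance.

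Section 8.1 does neither, and it does not say which effect the 25% is. The stated 80% is therefore not the power of the planned analysis under a defined assumption. That matters when a neutral result is read, since it must be clear what ITT difference the trial was built to detect. It also matters for the closed DSMC review of standard-care event rates announced in section 8.1, which needs a defined target difference to refer to.

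**Working it through.** **Inputs (protocol 8.1, 6.5, 8.2, Appendix VII).** Group B rate pB = 0.19; Group A rate pA = 0.1425; difference 0.0475; two-sided alpha 0.05; power 80%; 1:1 allocation; drop-out 5%; crossover 5%, from Group B to earlier angiography; CABG 8%; 1157 randomised per arm.

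**Step 1. Reproduce 964.** With pooled variance and no continuity correction,

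n = [1.960 × √(2p̄(1−p̄)) + 0.842 × √(pA(1−pA) + pB(1−pB))]² / (pB − pA)²

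p̄ = 0.16625, so 2p̄(1−p̄) = 0.27722, with root 0.52652. The separate variances sum to 0.12219 + 0.15390 = 0.27609, with root 0.52545.

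n = (1.0320 + 0.4422)² / 0.0475² = 2.1732 / 0.002256 = 963.2, rounded up to 964. The protocol's figure is right.

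**Step 2. Reproduce 1157.** 964 × 1.20 = 1156.8, rounded up to 1157. Drop-out alone gives 964/0.95 = 1014.7, or 1015. The other 1157 − 1015 = 142 per arm are there for crossover and CABG.

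**Step 3. Evaluable patients.** 1157 × 0.95 = 1099 per arm.

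**Step 4. Arm-level rates under each assumption.**
- If 5% of Group B cross over and gain the full effect: pB = 0.19 − 0.05 × 0.0475 = 0.1876.
- If the 8% having CABG gain nothing from timing: pA = 0.1425 + 0.08 × 0.0475 = 0.1463.

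**Step 5. Power at 1099 per arm.** Power = Φ([(pB − pA) − 1.960 × SE0] / SE1), where SE0 = √(2p̄(1−p̄)/1099) and SE1 = √([pA(1−pA) + pB(1−pB)]/1099).

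For the first case: (0.0475 − 1.960 × 0.01588)/0.01585 = 1.033, giving 84.9%.

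| Assumption | Group B | Group A | Relative reduction | Power | Evaluable per arm for 80% | Randomised per arm (÷ 0.95) |
|---|---|---|---|---|---|---|
| 25% is the ITT effect | 19.00% | 14.25% | 25.0% | 84.9% | 964 | 1015 |
| 5% of B cross over | 18.76% | 14.25% | 24.1% | 81.4% | 1062 | 1118 |
| 8% CABG, no timing effect | 19.00% | 14.63% | 23.0% | 78.2% | 1149 | 1210 |
| Both | 18.76% | 14.63% | 22.0% | 73.8% | 1278 | 1346 |

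**Step 6. Why a head-count does not cover dilution.** In the last row the remaining difference is 0.0413/0.0475 = 0.87 of the planned one. Treating 13% as losses multiplies n by 1/0.87 = 1.15. Dilution multiplies it by 1/0.87² = 1.32, and 964 × 1.32 is about 1274, close to the 1278 from the full formula.

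**The case against.** The strongest reply is that section 8.1 already works with the arm-level contrast. It states predicted rates for Group A and Group B as wholes and takes its starting point from group rates in a trial of early versus delayed intervention (13.9% versus 21.0%). Section 6.5 also frames the hypothesis as a strategy of immediate angiography. On that reading the extra 142 per arm are spare margin and power is about 85%. CABG counts as revascularisation in section 7.8, so surgical patients do receive the strategy. If only the documented Group B crossover dilutes the effect, power is still about 81%. The word conservative also has a basis: 25% was planned against an observed 35%.

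All of this stands as a possible reading, and it rules out a flat claim that the trial is underpowered, which a reader might infer from the 74% row. But the protocol does not commit to it. It makes a CABG allowance and explains it in Appendix VII by patients being referred for surgery instead of PCI. The section 8.1 table labels the arms as PCI groups, and Appendix VII describes the treatment-received comparison as the hypothesis actually under test. An allowance for CABG makes sense only if those patients are thought not to share the effect, and then a head-count is the wrong allowance.

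Three further inferences are not supported:

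- **Power near 50%.** Appendix VI says: "It is expected that approximately two-thirds of patients in our cohort will require PCI". Taking zero effect in everyone else leaves two thirds of the difference (19% versus 15.83%) and power of about 50%. No passage says that patients without PCI gain nothing from immediate angiography, so this is at most a labelled sensitivity case.
- **A contradiction with Appendix VII.** That appendix says "some (a few %) will have normal coronary arteries and others will need to be treated medically". The small percentage covers normal arteries only. With about 8% CABG and an unquantified medically treated group, the total can reach one third.
- **An error in 1157 itself.** Applying the three allowances in sequence gives 964/(0.95 × 0.95 × 0.92) = 1161, a difference of four patients per arm, with no material effect on power.

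**Conclusion.** The concern holds as a mismatch between the inflation method and the ITT analysis, together with an effect size whose target population is not stated. The 964 is correct. The step to 1157 handles two groups that stay in the analysis as if they left it.

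Power at the planned size is about 85% if 25% is the ITT effect, about 81% with 5% Group B crossover, and about 74% if CABG patients are also assumed to get no timing effect. These figures assume 5% loss in each arm, crossover in the one direction that the protocol describes, full benefit in those who cross over, and additive dilution. The zero timing effect in CABG patients is an assumption that the protocol's allowance suggests but does not state. Severity is moderate: whether power is above or below 80% turns on a choice that the protocol leaves open.

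**What to change.** Keep the total at 2314 and rewrite the end of section 8.1:

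1. Apply head-count inflation for the 5% drop-out only (964 to 1015 per arm), and state that 1157 per arm will be recruited, about 1099 of them evaluable.
2. State whether the 25% reduction is the ITT effect of the strategy or the effect in patients treated as assigned.
3. Restate the power for that choice: about 85% for the ITT effect, or about 74% to 81% under the listed dilution assumptions, naming each one.
4. Qualify the description of the calculation as conservative and robust so that it matches. Choosing 25% over the observed 35% can still be called conservative on effect size.

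A case for patients who receive no PCI may be added if it is labelled as a sensitivity analysis. The SAP was not available for this review; if it repeats the calculation, the same text belongs there. The cost is a short rewording and possibly a less favourable stated power. There are no extra patients and no change to the endpoint, the analysis or the conduct of the trial.
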